**Trial registration number:**

NCT04597710

Strengths and limitations of this studyPrecision1 will be the first study examining the clinical utility of radiogenomic information during the surgical treatment planning stage for patients with primary and secondary liver cancer.Our prospective study is designed to allow us to understand the extent to which quantitative MRI of the liver impacts surgical treatment planning.The additional value of whole genome sequencing will be evaluated to help us identify the presence of any clinically actionable genetic biomarkers which may support precision medicine provision to patients.All patients being considered for liver resection may be eligible for the study, regardless of tumour type or clinical background.The primary limitation of this study is the omission of a tightly matched negative control group where the impact of quantitative imaging on improving patient outcomes could be rigorously examined.

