## Methods and analysis

### Study design

A prospective observational cohort study.

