### Patient population

Patients who are due to undergo surgery for suspected liver tumour (primary or secondary). A sample size of up to 200 participants will be recruited from HHFT.

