### Clinical assessment

Minimal medical history data will be collected including information regarding previous diagnosis of liver cancer, cirrhosis and comorbidities including chronic kidney disease and diabetes. Information about alcohol consumption, smoking and coffee intake will be collected. Information about any recent chemotherapy regimens will be collected.

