### Magnetic resonance imaging

Current routine clinical practice requests patients to visit the hospital 3 days prior to the planned surgery date for a COVID-19 test. At this visit, participants will be invited for an abdominal non-contrast enhanced MRI scan. Images will be processed to generate metrics indicating the liver tissue characteristics (Liver*MultiScan*) and future liver remnant volume (Hepatica) as previously described.^12^

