### Whole genome sequencing

Genetic information from tumour tissue and from participant blood sample will be examined. A case review of all participants will be performed with these data to evaluate the clinically actionable information and what steps would have been taken by the clinical care team if this information were available prior to the operation.

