### Statistical analysis plan

The data will be evaluated to address the primary endpoint to calculate the proportion of patients in which the results from WGS would have resulted in a change in clinical management. The change in intended management after WGS results will be modelled as a binary variable on the basis of a binomial distribution.

From the literature, we estimate a prevalence of actionable biomarkers derived from genetics of 31%. Using a 5% allowable margin of error and 95% CI, a sample of 200 is required to give a reliable sample to achieve a change in management of 25% of patients.

Descriptive statistics will be reported for all endpoints specified and any interim analyses. Normality of the data will be determined by use of the Shapiro-Wilk test and visual study of histograms. Results will be expressed as mean with SD for continuous normally distributed variables, as median and IQR for non-normally distributed data and as counts and/or percentages for categorical variables. Linearity of continuous data will be assessed by scatter plots. To explore any potential systematic biases, categorical and demographic characteristics expressed as number (%) will be compared using χ^2^. For all tests, a p<0.05 will indicate statistical significance.

Correlations between results from Liver*MultiScan*/Hepatica-derived quantitative MRI metrics and histological features, as well as results from Liver*MultiScan* and genomic features will be determined with Spearman’s rank correlation coefficient and diagnostic performance will be assessed by the calculation of the receiver operating characteristic curve and the determination of the area under the receiver operating characteristic curve with 95% CIs. For all tests, a p<0.05 will be taken to indicate statistical significance.

To explore the impact of genetic variants associated with liver disease, the liver MR-derived biomarkers in those with and without known genetic variants associated with liver disease will be compared using a paired t-test (or non-parametric alternative).

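### A paired t-test is named for comparing MRI biomarkers between participants with and without liver-disease variants, but these are different people and the plan creates no pairs

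*Protocol article*

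**What the plan says.** The aim of the comparison is given in the Statistical analysis plan section of the protocol article: "To explore the impact of genetic variants associated with liver disease". The method follows in the same sentence: the MR-derived liver biomarkers "in those with and without known genetic variants associated with liver disease will be compared using a paired t-test (or non-parametric alternative").

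The rest of the article shows what data this test would receive:

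- Study design: "A prospective observational cohort study".
- Magnetic resonance imaging: at the hospital visit shortly before surgery, "participants will be invited for an abdominal non-contrast enhanced MRI scan". The Figure 1 caption places the MRI at study visit 1 and describes study visit 2, at twelve months, as a telephone interview.
- Whole genome sequencing: "Genetic information from tumour tissue and from participant blood sample will be examined".
- Patient population: "A sample size of up to 200 participants will be recruited from HHFT".
- Strengths and limitations: the main limitation is the "omission of a tightly matched negative control group".

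The Statistical analysis plan section also applies a 5% significance threshold to all tests.

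**The concern.** A paired t-test works on one difference per pair, so each value in one group must be linked to a particular value in the other. The link can come from two measurements on the same person or from deliberate matching. Having or lacking a variant divides the cohort into separate sets of people, and the article supplies neither kind of link.

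The bracketed alternative does not help. In context it covers data that fail the normality check. The usual non-parametric counterpart of a paired t-test is the Wilcoxon signed-rank test, which has the same requirement.

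At stake is whether the named analysis can be carried out at all, and whether two analysts following the text would reach the same answer. This is the only between-group test that the article specifies for the effect of liver-disease variants on MRI biomarkers, and the Introduction presents the integration of sequencing with imaging as the innovation of the project.

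**Working it through.** The plan states no figure for this comparison, so there is none to reproduce. The check has two parts: whether the design produces pairs, and what would follow if pairs were made up.

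**1. Does the design produce pairs?**

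- *Repeated scans.* There is one study MRI per participant, and visit 2 is a telephone call. There is no second MRI value to subtract.
- *Two genomes per person.* Tumour and blood are both sequenced, but the outcome compared is the liver MRI biomarker, and each participant has one study scan. Two genetic samples do not produce two linked MRI values.
- *Matching.* No section matches participants with a variant to those without. The limitation about a matched control group concerns the effect of imaging on outcomes, so it does not settle this point, but it supplies no matching either.

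Result: two independent groups. Given 40 values in one group and 160 in the other, a standard paired t-test routine stops with an error.

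**2. What if pairs were formed arbitrarily?**

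Input from the article: at most 200 participants and a 5% level. Assumptions: two-sided testing, normal data, SD 1 in both groups, a true difference of 0.5 SD, complete data on 200, and the group splits shown below.

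The standard error of the mean difference, in SD units, with group sizes n1 and n2 and m = min(n1, n2), is:

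- independent groups: √(1/n1 + 1/n2)
- m arbitrary pairs: √(2/m), because unrelated people contribute no correlation that would reduce the variance.

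For 40 against 160:

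- independent: √(1/40 + 1/160) = √0.03125 = 0.177, and 0.5/0.177 = 2.83
- arbitrary pairs: √(2/40) = √0.05 = 0.224, and 0.5/0.224 = 2.24
- participants unused: 200 − 2 × 40 = 120.

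Simulated power, with 20,000 data sets per split:

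| Split (assumed) | Unused if paired | Paired, arbitrary | Welch |
|---|---|---|---|
| 20 / 180 | 160 | 32% | 53% |
| 40 / 160 | 120 | 58% | 80% |
| 62 / 138 | 76 | 79% | 90% |
| 100 / 100 | 0 | 94% | 94% |

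A separate simulation of 4,000 data sets gave 59% and 80% at 40/160. The analytic two-sample power formula gives 56%, 81%, 90% and 94% for the independent comparison.

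With no true difference, the arbitrary paired test rejected in 4.8% to 5.2% of data sets across the four splits.

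**3. Dependence on the pairing.** One simulated data set (40 against 160) was paired at random 5,000 times. The central 95% of the paired p-values ran from 0.005 to 0.84, with median 0.15. The Welch test on the same data gives a single value, 0.056.

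**The case against.** The strongest reply is that this is a wording slip, probably for *unpaired*, in one exploratory comparison. The comparison is neither the primary endpoint nor one of the five listed secondary endpoints, and the sample size does not rest on it. An analyst with unequal groups would find the test will not run and would correct it. The same section also plans Spearman correlations between LiverMultiScan results and genomic features. For a binary variant, that amounts essentially to a rank comparison of the two groups, so the scientific question does not hang on the t-test alone. All of this stands and limits the importance of the point. It does not make the named test applicable.

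A reader might infer three stronger points, which the document does not support:

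- *That the test would inflate false positives.* It would not: the error rate under arbitrary pairing stays near 5%. The test is inapplicable to unpaired groups, not anti-conservative.
- *That the study will lose the power shown in the table.* Those losses arise only if someone invents pairs and discards the surplus, which the article does not propose. The split, the effect size and complete data on 200 are also assumptions. The article says up to 200 and applies listwise deletion.
- *That the comparison must be adjusted for the lifestyle and treatment data collected.* The Clinical assessment section does say "Information about alcohol consumption, smoking and coffee intake will be collected. Information about any recent chemotherapy regimens will be collected", but a condensed article may leave covariates to a fuller plan. Nor is it evident that these factors confound variant status. Body mass index or diabetes could lie on the path from variant to liver fat, and adjustment could then remove part of the effect being explored.

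**Conclusion.** Wrong as written, with moderate importance. The article names a test that needs linked observations for two groups of different people, and neither the schedule nor any matching provides links. This conclusion rests only on the text and needs no assumption about carrier frequency or effect size.

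The practical size is bounded. With unequal groups the test cannot be run. With invented pairs the answer is arbitrary and, under the assumed 0.5 SD difference, power falls by about 21 percentage points at 20/180, 22 at 40/160, 11 at 62/138, and essentially not at all with equal groups. These figures are illustrations of a hypothetical analysis. The primary endpoint is unaffected.

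**What to change.** In the Statistical analysis plan section, replace the paired t-test and its unspecified alternative with an independent-samples (Welch) t-test, or the Wilcoxon rank-sum test if the biomarker is not normally distributed. If pairing was really intended, state instead how participants with and without a variant are to be matched and on which characteristics.

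The cost of the first option is one sentence of wording. It needs no extra data, visits or participants, and it can be made before the comparison is run.

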### Patient and public involvement

No formal patient advisory committee was set up and there was no patient or public involvement in the design and planning of the study. A patient and public involvement and engagement group has been assembled and will be consulted during dissemination of the findings.
